## Abstract

Faecal microbiota transplantation (FMT) is an emerging therapy for gastrointestinal and neurological disorders, acting via the microbiota–gut–brain axis. Altering gut microbial composition may influence cognitive function, but this has not been tested in cognitively healthy adults. This randomised, double-blinded, placebo-controlled pilot trial investigates whether FMT is feasible and improves cognition in adults with irritable bowel syndrome (IBS). Participants receive a single dose of FMT or placebo via rectal retention enema. Cognitive performance is the primary outcome, assessed using the Cambridge Neuropsychological Test Automated Battery (CANTAB). Secondary outcomes include IBS symptom severity and mood. Tertiary outcomes include microbiome composition and plasma biomarkers related to inflammation, short-chain fatty acids, and tryptophan metabolism. Outcomes are assessed at baseline and at one, three, six, and twelve months following treatment. We hypothesise that FMT will lead to greater improvements in cognitive performance than placebo, with benefits extending beyond practice effects, emerging at one month and persisting in the long term. The findings will contribute to evaluating the safety and efficacy of FMT and enhance our understanding of gut–brain interactions.

## 1. Introduction

Faecal microbiota transplantation (FMT) is a gut-microbiome-altering therapy used as a standardised treatment for recurrent *Clostridioides difficile* infections (rCDI) when antibiotics fail. FMT has been demonstrated to be generally safe and well tolerated [1]. Recent research suggests that FMT might be a promising treatment for various conditions beyond rCDI, including inflammatory bowel disease, cirrhosis, and neurological conditions like Parkinson’s disease and dementia [1].

In adults with neurodegenerative diseases, an aberrant microbiome profile has been found, suggesting a link between neurodegeneration and changes in gut microbial composition [2]. FMT may influence the gut microbiome [3], thereby potentially impacting the microbiota–gut–brain axis, a multi-pathway system allowing for bidirectional communication between the brain and the gut and its resident micro-organisms [4]. This interaction may contribute to cognitive enhancement in patients with neurological conditions [5,6,7].

While most clinical studies report changes in the composition of the gut microbiome following FMT [5,7,8], these changes are sometimes accompanied by changes in the blood biomarkers for inflammation and bile acid profile [5,8]. However, the exact mechanisms underlying improvements in cognition remain unclear. FMT studies in humans have noted a reduction in pro-inflammatory cytokine interleukin-6 (IL-6) levels [8,9], a reduction in acute-phase lipopolysaccharide-binding protein [8], and a reduction in primary along with an increase in secondary bile acid levels [9] (see Figure 1).

Several microbial taxa have been linked to cognitive function and gut–brain axis signalling, supporting the biological plausibility of interventions such as FMT. The two key pathways thought to mediate microbiota–brain interactions are short-chain fatty acid (SCFA) production and tryptophan metabolism [4]. Genera such as *Lactobacillus* and *Bifidobacterium* have been associated with better cognitive performance [10,11] and are the key producers of short-chain fatty acids (SCFAs) [12]. Altered SCFA levels have been linked to various neurological disorders [13]. In individuals with IBS, changes in SCFA concentrations following FMT have been shown to persist for over one year [14].

Furthermore, *Lactobacillus reuteri* has been shown to influence the kynurenine pathway [15], a tryptophan-derived metabolic route implicated in cognitive outcomes [16]. More broadly, the gut microbiome has also been shown to modulate the metabolism of tryptophan to kynurenine [17], potentially through modulation of the inflammatory mediators [18] that regulate kynurenine metabolism [19]. An increased kynurenine-to-tryptophan ratio has been associated with cognitive impairment [16], and probiotics have been found to modulate this ratio [20]. Together, these microbial pathways, SCFA production and tryptophan metabolism, represent compelling targets for monitoring in this study, given their potential links to cognitive function and the gut-rain axis.

Preclinical studies further support the notion that FMT modifies bowel microbial composition and inflammation [21]. Notably, transferring FMT from old donor mice into young mice leads to an increase in pro-inflammatory cytokines in the latter, while transferring FMT from young donor mice into old recipient mice decreases circulating pro-inflammatory cytokines [22]. Additionally, in a transgenic Alzheimer’s disease (AD) mouse model (5xFAD), FMT could rescue object recognition performance assessed via the novel object recognition test and could improve spatial memory in a forced alternation Y-maze task. Furthermore, a reduction was observed in cortical amyloid beta after FMT compared to untreated controls [23].

**Figure 1 mps-08-00083-f001:**
[figure not shown]
Effect of FMT on systemic circulation markers. Schematic representation of proposed changes in systemic biomarkers in the circulatory system which may influence the brain following faecal microbiota transplantation. IL-6 = interleukin-6, LBP = lipopolysaccharide-binding protein. Created in BioRender [24].

Studies in cognitively healthy individuals have explored the effects of pre- and probiotics on cognitive function and found improvements in memory and processing speed [25]. However, some studies also report declines in cognitive function [26], which implies that microbial changes are not always beneficial in cognitively healthy adults. Beyond bacteria, the gut virome, predominantly consisting of bacteriophages, appears to influence executive function and memory [27]. Furthermore, the composition of the gut mycobiome, the small fungal component of the gut microbiome, has been found to differ in people with mild cognitive impairment compared to healthy human controls [28]. Unlike other microbiome alteration techniques, such as pre- and probiotics, FMT not only targets the bacterial composition but also the gut virome and mycobiome [29], offering a more comprehensive intervention.

To the best of our knowledge, no studies have examined the cognitive effects or safety of FMT in cognitively healthy adults. Given that FMT has been shown to alter the gut bacteriome, virome, and mycobiome [29], we hypothesise that FMT has the potential to modulate cognitive function compared to placebo. Probiotic studies have shown an effect on cognition as early as four weeks following intervention [30]. Therefore, we chose our first two follow-up visits to be at one month and three months following intervention. To investigate the potential long-term effects on the microbiome, blood markers, and cognitive function, we included follow-up visits at six months and twelve months.

Our study looks at a subsample of participants who receive a single 60 g dose of FMT or placebo via rectal retention enema as part of a broader investigation into the efficacy of FMT in irritable bowel syndrome (IBS), a prevalent gut–brain axis disorder [31]. The first-line treatment of care for IBS is dietary change, especially the low fermentable, oligosaccharide-, disaccharide-, monosaccharide-, and polyol (FODMAP) diet [32], in addition to over-the-counter medication, such as laxatives and loperamide [33]. FODMAPs are short-chain carbohydrates, which can exacerbate IBS symptoms, and restricting their intake has been found to improve symptoms [34]. While IBS symptoms include abdominal pain accompanied by changes in stool frequency or form [31], individuals with IBS have been found to perform similarly to healthy controls on neuropsychological screenings of cognitive function [35], making this a suitable cohort for investigating subtle cognitive modulation.

Only participants who do not significantly improve following the low FODMAP diet will be included. The selected FMT dose has shown efficacy in IBS [36], and rectal delivery was chosen for its superior effectiveness in rCDI [37] and ulcerative colitis [38], with enemas being less risky than colonoscopy [39]. Continued use of standard IBS medications during the trial is permitted, justifying the use of a placebo control.

This article was previously presented as a meeting abstract at the Australasian Neuroscience Society 2024 Annual Scientific Meeting on the 4th of December 2024.

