To confirm eligibility, potential participants will be screened for cognitive health using the MoCA and then referred to a study dietitian for a one-on-one, one-hour education session on the low FODMAP diet. Participants will then follow the diet for 21 days under dietitian supervision. Adherence is monitored through daily food diaries, submitted weekly and reviewed via phone consultation. Participants are encouraged to contact the study team with any diet-related questions. Adherence is calculated as the percentage of meals compliant with the low FODMAP guidelines, based on food diaries, and it is considered successful if more than 80% of meals meet the criteria. The IBS-SSS will be completed before starting the diet and on the final day of the diet. If participants achieve less than a 50-point reduction on the IBS-SSS and a MoCA score of 26 or more, they are deemed eligible for participation in this trial.

At the baseline visit, eligible participants will provide informed consent and complete the Cambridge Neuropsychological Test Automated Battery (CANTAB), the Depression Anxiety Stress Scale (DASS-42), IBS-SSS, and the IBS Quality of Life questionnaire (IBS-QoL).

Following baseline assessment, participants will be randomised to receive a single rectal retention enema containing either FMT or placebo using the National Cancer Institute Clinical Trial Randomization Tool, applying a maximum tolerated imbalance of two. The enema will consist of a 60 mL dose and will be administered by a gastroenterologist with the participant lying in the left lateral position, followed by a 20 min monitoring period. FMT and placebo materials will be prepared in advance in accordance with the Australian Therapeutic Goods Administration (TGA) (Therapeutic Goods Order 105/107) guidelines, and syringes will be labelled by a researcher not involved in data collection or intervention delivery to ensure blinding of participants, clinicians, and research staff.

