## 3. Procedure

### 3.1. Intervention Preparation

Screen potential stool donors according to TGA Therapeutic Goods Order 105 for eligibility.Collect stool in a sterile bucket within 6 h after defaecation.Weigh stool.Mix stool with phosphate-buffered saline and ten per cent pharmaceutical-grade glycerol to reach a ten percent concentration of stool.Draw the resulting faecal suspension into 60 mL syringes labelled according to TGA Therapeutic Goods Order 107.Produce placebo by mixing glycerol and saline solution (ratio 5:1), 5 g fibre, and 2 mL food colouring per litre.Draw the resulting suspension into 60 mL syringes.Cover all syringes in aluminium foil to ensure blinding.Store at −80 °C.

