### 3.4. Intervention Visit (~1 h)

Thaw FMT or placebo syringes in an ice bath for two hours.Collect stool sample from participant and store at −80 °C.Provide participant with a fresh stool sampling kit for use before the follow-up visit.Administer 60 mL of the assigned treatment via rectal retention enema while the participant lies in a left lateral position.

 **PAUSE STEP** Ask participants to remain in the lateral position for 20 min under medical supervision to ensure adherence.

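### The stated 60 g FMT dose does not match the roughly 6 g of stool in the enema as prepared, and the article does not say what the 60 g measures

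*Protocol article*

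**What the plan says.** The dose is described in four places in the protocol article.

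- **Section 1 (Introduction, after Figure 1).** Participants "receive a single 60 g dose of FMT or placebo via rectal retention enema". The next paragraph says that the selected dose has shown efficacy in IBS and cites reference 36. It gives no mass, volume or concentration for that earlier work.
- **Section 2 (Experimental Design).** After baseline, "participants will be randomised to receive a single rectal retention enema containing either FMT or placebo", and "The enema will consist of a 60 mL dose".
- **Section 3.1 (Intervention Preparation).** Stool is weighed, then mixed with buffered saline and glycerol "to reach a ten percent concentration of stool". The next step is: "Draw the resulting faecal suspension into 60 mL syringes". The placebo is made from glycerol, saline, fibre and food colouring, with no stool.
- **Section 3.4 (Intervention Visit).** "Administer 60 mL of the assigned treatment via rectal retention enema".

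The 60 g figure appears once, in the Introduction. The article does not say whether it is stool or finished suspension, and does not say whether ten percent is by weight or by volume. It describes no step that concentrates the stool and no repeat enema. Section 3.4 speaks of thawing syringes in the plural, but then fixes the amount given at 60 mL.

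**The concern.** A reader who takes the Introduction at face value will believe that each FMT participant receives 60 g of donor stool, at a dose with prior evidence in IBS. A reader who works from the preparation steps will arrive at about a tenth of that mass. The article prints mass, concentration, volume and number of administrations, so this is a disagreement among its own figures and not a detail left to a fuller protocol.

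Stool mass is the exposure under test, and it is given once. Section 2 says that the pilot is to provide preliminary effect-size estimates and to inform the design and sample size of a larger trial. An effect estimate is of use for that purpose only if it is tied to the exposure that produced it. If 60 g is carried into the results as stool mass when about 6 g was given, a favourable signal would be attached to the wrong dose in the next trial. An unfavourable one could be read as bearing on a dose that was not given.

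**Working it through.** **Inputs from the article**

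- Stated dose: 60 g, single (Section 1).
- Enemas per participant: 1 (Section 2).
- Volume given: V = 60 mL (Sections 2 and 3.4; syringe size in Section 3.1).
- Stool concentration: 10%, basis not stated (Section 3.1).

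**Assumed input.** The article gives no density for stool or suspension. I take 1.00 to 1.06 g/mL.

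**Step 1. Try to reproduce 60 g as stool mass.** Stool mass = volume × concentration, under each plausible meaning of ten percent:

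| Reading of ten percent | Calculation | Stool mass | 60 g ÷ stool mass |
|---|---|---|---|
| Weight per volume | 60 × 0.10 | 6.0 g | 10.0 |
| Weight per weight, density 1.00 | 60 × 1.00 × 0.10 | 6.0 g | 10.0 |
| Weight per weight, density 1.03 | 60 × 1.03 × 0.10 | 6.2 g | 9.7 |
| Weight per weight, density 1.06 | 60 × 1.06 × 0.10 | 6.4 g | 9.4 |
| Volume per volume, stool density 1.06 | 60 × 0.10 × 1.06 | 6.4 g | 9.4 |
| One part stool to ten parts diluent | 60 ÷ 11 | 5.5 g | 11.0 |

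The figure is not reproduced. Every reading gives 5.5 to 6.4 g, so the undefined basis of the percentage does not explain the gap.

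**Step 2. Ask what would have to be true for 60 g of stool** (for comparison only, not as a proposal).

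- At 10% weight per volume: 60 g ÷ 0.10 g/mL = 600 mL, which is 600 ÷ 60 = 10 syringes.
- In 60 mL: 60 g ÷ 60 mL = 1 g/mL, which is 100% weight per volume.

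Neither is described in the article.

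**Step 3. Try to reproduce 60 g as the weight of the whole suspension.** Weight = 60 mL × density: 60.0 g at 1.00, 61.8 g at 1.03 and 63.6 g at 1.06 g/mL. The figure is recovered, exactly or within a few percent. On this reading the stool content is still that of Step 1, about 6 g.

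**The case against.** The best reply is that 60 g was never meant as stool mass. The sentence applies the same 60 g to FMT and to placebo, and the placebo contains no stool. Read that way, it describes the weight of the product in the syringe, which parallels the 60 mL stated for both arms in Section 2. Step 3 shows that the two then agree. It could equally be a slip of unit for 60 mL. This stands. A reader might infer that the four sections cannot all be true, or that the stated dose is undeliverable. That holds only if 60 g is stool mass, and the article does not say so.

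Two other strong readings also fail. A reader might infer that the trial gives a tenth of a dose known to work. The article does not state the dose used in reference 36, and that source is not at hand, so the comparison cannot be made. A reader might also infer that the site could prepare either amount. Sections 2, 3.1 and 3.4 agree with one another, and none of them mentions 60 g. Staff who follow the procedure have one product to make.

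It can also be said that Section 2 limits what a null result could mean: the pilot is not powered for small or moderate effects, and the single dose is listed as a limit on generalisability. This tempers the consequence. It does not remove the need to know which exposure the estimates belong to.

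What the reply does not rescue is the description of exposure. If 60 g is product weight or a slip, the only dose mass in print is about ten times the stool content, and the efficacy statement rests on a selected dose whose unit is undefined.

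**Conclusion.** The point holds in this form: the article's central exposure is either contradicted or left ambiguous by a factor of about ten (9.4 to 11). By its own preparation and volume, one enema holds about 6 g of stool, and the Introduction prints 60 g without saying of what. The result rests on the printed volume, concentration and single administration, and on an assumed density of 1.00 to 1.06 g/mL, which moves the answer only between 5.5 and 6.4 g.

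Confidence is high in the arithmetic and in the need to reconcile. There is no basis for saying which of the mass, the volume, the concentration or the unit is in error, nor that the dose given differs from the one in the cited study.

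**What to change.** 1. Reconcile Sections 1, 2, 3.1 and 3.4 so that stool mass, concentration (with its basis: weight per volume, weight per weight or volume per volume) and volume per participant agree. State whether any mass quoted is stool or finished suspension. Do not presume in advance which figure is wrong. Which dose is right is for the sponsor.
2. Keep the statement that the selected dose has shown efficacy in IBS only if the sponsor confirms that the cited study used the reconciled stool mass. Otherwise withdraw or reword it.
3. Report the stool mass delivered, derived from the weighing already in Section 3.1, so that the pilot's effect estimates are attached to the dose actually given.

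The cost is a change of protocol wording, a look at the cited source and a check of preparation records. It needs no additional participants, visits or procedures.

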## 2. Experimental Design

Study visits will take place at Macarthur Clinical School in Campbelltown and the NICM Health Research Institute in Westmead. The intervention will be administered at Campbelltown Private Hospital. All sites are affiliated with Western Sydney University. This study is a sub-study of a larger clinical trial registered with the Australian New Zealand Clinical Trial Registry (ACTRN12623000353695) in accordance with the World Health Organization Trial Registration Data Set (see Supplementary File S1). While the main trial focuses on IBS symptom severity, the present sub-study investigates cognitive outcomes as the primary endpoint.

Participants will be eligible for inclusion if they are aged 18 years or older and meet the ROME IV criteria for IBS, defined as recurrent abdominal pain occurring at least once per week over the past three months, accompanied by at least two of the following: pain related to defaecation, changes in stool frequency, or changes in stool form. Normal cognitive function is defined as a score of ≥26 in the Montreal Cognitive Assessment (MoCA). Only individuals who fail to respond to a dietician-guided low FODMAP diet—defined as a reduction of less than 50 points on the IBS Symptom Severity Score (IBS-SSS) after 21 days—will be included.

The exclusion criteria include gastrointestinal or neurological comorbidities, MoCA < 26, significant symptom reduction after the low FODMAP diet (≥50 points), pregnancy or lactation, a history of abdominal surgery (except appendectomy, cholecystectomy, caesarean section, or hysterectomy), severe psychiatric illness, active gastroenteritis, recent use of antibiotics or probiotics (within eight weeks), use of IBS-specific medications within the past three months (except polyethylene glycol or loperamide), and substance misuse.

As part of the sub-study, we aim to recruit 20 participants, with 10 allocated to the FMT group and 10 to the placebo group. The first 20 participants enrolled in the overarching trial will be recruited into this sub-study and will complete additional cognitive tests and questionnaires at all study visits. Recruitment will take place through the gastroenterology outpatient clinic at Campbelltown Hospital, a Meta-advertisement campaign run by Western Sydney University, and a university-maintained database of participants from a previous IBS clinical trial.

To confirm eligibility, potential participants will be screened for cognitive health using the MoCA and then referred to a study dietitian for a one-on-one, one-hour education session on the low FODMAP diet. Participants will then follow the diet for 21 days under dietitian supervision. Adherence is monitored through daily food diaries, submitted weekly and reviewed via phone consultation. Participants are encouraged to contact the study team with any diet-related questions. Adherence is calculated as the percentage of meals compliant with the low FODMAP guidelines, based on food diaries, and it is considered successful if more than 80% of meals meet the criteria. The IBS-SSS will be completed before starting the diet and on the final day of the diet. If participants achieve less than a 50-point reduction on the IBS-SSS and a MoCA score of 26 or more, they are deemed eligible for participation in this trial.

At the baseline visit, eligible participants will provide informed consent and complete the Cambridge Neuropsychological Test Automated Battery (CANTAB), the Depression Anxiety Stress Scale (DASS-42), IBS-SSS, and the IBS Quality of Life questionnaire (IBS-QoL).

Following baseline assessment, participants will be randomised to receive a single rectal retention enema containing either FMT or placebo using the National Cancer Institute Clinical Trial Randomization Tool, applying a maximum tolerated imbalance of two. The enema will consist of a 60 mL dose and will be administered by a gastroenterologist with the participant lying in the left lateral position, followed by a 20 min monitoring period. FMT and placebo materials will be prepared in advance in accordance with the Australian Therapeutic Goods Administration (TGA) (Therapeutic Goods Order 105/107) guidelines, and syringes will be labelled by a researcher not involved in data collection or intervention delivery to ensure blinding of participants, clinicians, and research staff.

Stool donors will be screened in accordance with TGA guidelines (Therapeutic Goods Order 105) for human intestinal microbiota transplants. Eligible donors are healthy adults with no history of chronic gastrointestinal disorders, infectious diseases, recent antibiotic use, or high-risk behaviours. Screening includes a detailed social and medical history, physical examination, and laboratory testing of both blood and stool samples. Blood tests include screening for HIV-1 and HIV-2, hepatitis A, B, and C, syphilis, HTLV-I/II, and other transfusion-transmissible infections. Stool samples are tested for common enteric pathogens, including *Clostridioides difficile*, *Salmonella*, *Shigella*, *Campylobacter*, *Giardia*, *Cryptosporidium*, and norovirus, as well as for antimicrobial-resistant organisms, such as extended-spectrum beta-lactamase-producing bacteria. Donors are also screened for COVID-19. All screening procedures are repeated every 90 days during the donation period.

Participants will return for follow-up assessments at one, three, six, and twelve months following treatment (see Figure 2). At each time point, they will complete all questionnaires and cognitive tests and provide stool and blood samples.

This pilot trial will assess the feasibility of the protocol and provide preliminary estimates of the effect size. Cognitive performance, inflammatory markers, and microbial metabolites will be analysed using mixed-design ANOVA, with group (FMT vs. placebo) as the between-subjects factor and time (baseline, one, three, six, and twelve months) as the within-subjects factor. Planned contrasts will examine within-group changes over time. Microbiome composition will be compared using PERMANOVA with Bray–Curtis dissimilarity, and missing data will be addressed using multiple imputation.

Participants are advised to contact the trial coordinator if they experience any side effects. Although FMT is generally safe and well tolerated, minor adverse events, such as constipation, diarrhoea, or low-grade fever, may occur, typically resolving within 48 h. These will be reviewed by a gastroenterologist and documented in a password-protected file. A serious adverse event is defined according to Australian National Health and Medical Research Council guidelines as any event resulting in death, being life-threatening, requiring or prolonging hospitalisation, causing significant disability, or leading to a congenital anomaly. Serious adverse events will be monitored until resolution.

Due to the low-risk nature of this pilot study and the small sample size, a Data Safety Monitoring Board is not required. Participants in the placebo group who complete all follow-up visits will be offered FMT at the end of the trial, provided blinding is maintained until data collection is complete.

As a pilot study, this trial is not powered to detect small or moderate effects. The main aim is to assess the feasibility, test procedures, and to explore the potential signals of cognitive benefit to inform the design and sample size of a future large-scale trial. While all participants are carefully screened, individual variability in microbiota composition and baseline cognitive performance may affect outcomes. Additionally, the use of a single FMT dose and lack of dietary control following intervention may limit the generalisability of the results.

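### Baseline is analysed as one of five outcome times and only within-arm contrasts are named, so the between-arm hypothesis rests on a 4-df interaction with no single baseline-adjusted arm difference

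*Protocol article*

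**What the plan says.** All of this is in the protocol article.

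- **Model** (2. Experimental Design): cognition, inflammatory markers and microbial metabolites go into a mixed-design ANOVA. Its factors are set out thus: "with group (FMT vs. placebo) as the between-subjects factor and time (baseline, one, three, six, and twelve months) as the within-subjects factor".
- **Contrasts** (same section): "Planned contrasts will examine within-group changes over time". No between-arm contrast and no baseline covariate is named.
- **Missing data** (same section): "missing data will be addressed using multiple imputation".
- **Order of events** (same section): "Following baseline assessment, participants will be randomised to receive a single rectal retention enema containing either FMT or placebo". Baseline is therefore measured before allocation.
- **Size** (same section): "we aim to recruit 20 participants, with 10 allocated to the FMT group and 10 to the placebo group".
- **Hypothesis** (Abstract), on the expected result in the active arm: "greater improvements in cognitive performance than placebo, with benefits extending beyond practice effects, emerging at one month and persisting in the long term".
- **Deliverable** (2. Experimental Design): the pilot will "provide preliminary estimates of the effect size".

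**The concern.** Because randomisation follows the baseline visit, the true arm difference at that visit is zero. Once baseline is a level of time, the group main effect averages in a visit at which treatment cannot act. The term that compares change between arms is then the group-by-time interaction, which has (2−1)(5−1) = 4 degrees of freedom and asks only whether the two profiles differ in any way. The hypothesis is more specific: FMT above placebo, from month one, lasting. The named contrasts do not test it either, since each looks inside one arm, where practice effects and treatment are mixed.

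At stake is the main quantitative product of the pilot. An omnibus F test gives no arm difference with a confidence interval to carry into the design of a later trial, and with 20 participants an inefficient estimator is costly.

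**Working it through.** **Inputs from the article.** 10 per arm; five times, of which four follow treatment; baseline before randomisation; an effect hypothesised from month one and persisting.

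**Assumptions (the article gives none of these).** Two-sided alpha 0.05; SD 1 at each visit; constant post-treatment difference d = 0.8; compound symmetry with within-person correlation r; complete data. The article states no power figure, so there is none to reproduce.

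**Step 1. Group main effect.** Averaging five visits, one with no effect, gives 0.8d. Its variance is (2/10)(1+4r)/5, so the noncentrality is 16d²/(1+4r) on F(1,18).

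**Step 2. 4-df interaction.** The arm-difference profile (0, d, d, d, d), centred, is (−0.8d, 0.2d, 0.2d, 0.2d, 0.2d), with sum of squares 0.8d². Noncentrality = 20 × ¼ × 0.8d²/(1−r) = 4d²/(1−r) on F(4,72).

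**Step 3. 1-df change contrast (follow-up mean minus baseline, between arms).** Variance = 0.2 × 5(1−r)/4 = 0.25(1−r). The noncentrality is again 4d²/(1−r), now on F(1,18).

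**Step 4. Baseline-adjusted follow-up mean.** Variance = 0.2 × (1−r)(1+4r)/4 × (1+1/16), on F(1,17). The last factor is the cost of estimating the covariate slope with 20 people.

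**Power at d = 0.8**

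| r | Main effect | 4-df interaction | 1-df change | Adjusted mean |
|---|---|---|---|---|
| 0.5 | 0.417 | 0.381 | 0.572 | 0.761 |
| 0.6 | 0.376 | 0.470 | 0.668 | 0.801 |
| 0.7 | 0.343 | 0.604 | 0.789 | 0.865 |
| 0.8 | 0.315 | 0.802 | 0.922 | 0.946 |
| 0.9 | 0.293 | 0.986 | 0.998 | 0.998 |

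From interaction to change contrast only the degrees of freedom are saved. From change contrast to adjusted mean is the effect of adjustment.

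**Step 5. Variance effect of adjustment alone.**
- Follow-up average, relative to the change contrast: (1+4r)/5 × 17/16. At r = 0.5, 0.60 × 1.0625 = 0.64 (36% less). At 0.7, 0.76 × 1.0625 = 0.81 (19% less). At 0.9, 0.92 × 1.0625 = 0.98 (2% less).
- Single visit, such as month one: (1+r)/2 × 17/16. This is 0.85 at r = 0.6 (15% less), 0.90 at 0.7 (10% less) and 1.01 at 0.9 (no gain).

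**Step 6. Other effect shapes.** Simulation, 3,000 runs, r = 0.7, compound symmetry, no sphericity correction:

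| Effect at 1, 3, 6, 12 months | 4-df interaction | Adjusted average |
|---|---|---|
| Waning: 0.8, 0.8, 0.4, 0 | 0.71 | 0.48 |
| Late: 0, 0.3, 0.6, 0.8 | 0.60 | 0.37 |

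**Step 7. Missing follow-up.** With simulated missing-at-random dropout leaving about 15.4 of 20 completers (r = 0.7, correlation treated as known), the baseline-adjusted likelihood analysis without imputation averaged 0.803 for a true 0.80, with empirical SE 0.266. A completer-only change contrast had SE 0.312. That is not the article's plan, which imputes; the check shows only that the likelihood analysis was essentially unbiased without imputation.

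**The case against.** The strongest reply is that setting a 4-df omnibus test against a 1-df average is not like with like. A between-arm change contrast inside the planned ANOVA would recover much of the gap: at r = 0.7, power goes from 0.60 to 0.79, and adjustment adds the rest, to 0.87. This stands. But the article names no such contrast, only within-arm ones.

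Second, an omnibus profile test is defensible in an exploratory pilot. 4. Expected Results allows for improvement or variability under FMT, and Step 6 shows the interaction ahead for waning and late effects. This also stands, and it is why visit-specific differences must be kept. The Abstract nevertheless commits to a persisting effect.

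Third, the article disclaims power for small or moderate effects and puts feasibility first. That lowers the stakes. It does not remove the need for a usable effect estimate, since the results are meant to inform the size of a later trial.

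A reader might infer stronger faults, which the document does not support:

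- **That the ANOVA discards baseline.** It does not; the interaction compares change from it.
- **That the F test is anti-conservative.** Without correction, simulated type I error under AR(1) was 0.06 to 0.08; with Greenhouse–Geisser it was 0.04 to 0.05. The article is silent on correction, which commonly belongs in the analysis plan, so no fault follows.
- **That multiple imputation is an error or wholly unnecessary.** It is valid under missing-at-random, and classical ANOVA needs complete rows. A mixed model removes the need only for missing follow-up values of its own outcomes.

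**Conclusion.** The concern holds as a matter of efficiency and aim. The article fixes an analysis in which the between-arm hypothesis is carried by a 4-df interaction, the named contrasts do not compare arms, and no single baseline-adjusted arm difference is defined. Under a sustained d = 0.8, compound symmetry and r from 0.5 to 0.8, moving to a baseline-adjusted average raises power from 0.38–0.80 to 0.76–0.95. Naming a 1-df between-arm contrast supplies much of this; the share due to adjustment is large at r = 0.5 and almost nil at 0.9. For one month alone, adjustment gains about 10% to 15% in variance at r = 0.6 to 0.7. The size of the gain therefore rests on a correlation the article does not give and on an effect that persists. The analysis should be changed, but it is not invalid.

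**What to change.** Replace the ANOVA for the continuous outcomes by a linear mixed model for the four post-baseline visits, with arm, visit, arm-by-visit and the baseline value of the same outcome. Alternatively, keep baseline in the outcome vector with arm means constrained equal there. Choose a covariance structure suited to visits at 1, 3, 6 and 12 months (standard AR(1) assumes equal spacing) and use Kenward–Roger degrees of freedom.

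Prespecify two between-arm contrasts, at one month and averaged over follow-up, each with a 95% CI. Report the arm difference at every visit as well, so that a waning or late effect is not hidden by the average. Within-arm changes can stay as description.

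State that missing follow-up values of these outcomes are handled by likelihood under missing-at-random. Say separately how a missing baseline (if used as a covariate) and the PERMANOVA will be handled; multiple imputation may remain there.

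Cost: a wording change in the analysis section, with the same data and standard software. The drawback is lower power for the averaged contrast than for the interaction if the effect does not persist.
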